### High-intensity NPPV

In the high-intensity NPPV group, patients will undergo pressure-limited NPPV (e.g., NPPV in spontaneous/timed mode) at a higher IPAP level. IPAP is initially set at 10 cmH_2_O and continuously adjusted by increments and decrements of 1–2 cmH_2_O (up to 30 cmH_2_O), according to patients’ tolerance, to obtain a tidal volume (*V*_T_) of 15 mL/kg of predicted body weight (PBW). The PBW is calculated according to a predefined formula: 50 + 0.91 × (centimeters of height − 152.4) for men and 45.5 + 0.91 × (centimeters of height − 152.4) for women. IPAP should be increased as much as possible to decrease PaCO_2_ to a normal level. However, if PaCO_2_ decreases to less than 35 mmHg, IPAP should be decreased to achieve normocapnia.

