## Methods/design

### Aims

The primary aim of the HAPPEN study is to determine whether high-intensity NPPV is more effective for correcting hypercapnia than low-intensity NPPV in patients with AECOPD. The secondary aim is to determine whether high-intensity NPPV is more effective than low-intensity NPPV for decreasing PaCO_2_ from baseline to 2 h after randomization and hospital mortality, and improving 28-day mortality and 90-day survival.

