### Study population

During screening and prior to enrollment in the study, patients will be considered eligible for the study if they are diagnosed with AECOPD as defined by the criteria of the Global Initiative for Chronic Obstructive Lung Disease (GOLD) in 2017, with arterial pH < 7.35 and ≥ 7.25, and PaCO_2_ > 45 mmHg [1].

Patients will be excluded from study participation if any of the following criteria are present: age < 18 years; excessive amount of respiratory secretions or weak cough; upper airway obstruction; recent oral, facial, or cranial trauma or surgery; recent gastric or esophageal surgery; severe abdominal distension; active upper gastrointestinal bleeding; cardiac or respiratory arrest; pH < 7.25; arterial oxygen tension/fraction of inspired oxygen (PaO_2_/FiO_2_) < 150 mmHg; pneumothorax; severe ventricular arrhythmia or myocardial ischemia; severe hemodynamic instability despite fluid repletion and use of vasoactive agents; severe metabolic acidosis; lack of cooperation; and refusal to receive NPPV [29]. Patients will also be excluded if they have a do-not-intubate order or refuse research authorization.

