### NPPV weaning and failure

For all patients, the levels of IPAP and EPAP and the daily use of NPPV can be gradually decreased under conditions of clinical stability, defined as the presence of the following: the improvement or resolution of the underlying cause of AECOPD, RR < 25 breaths/min, heart rate < 110 beats/min, arterial pH < 7.35, and PaO_2_ > 60 mmHg at FiO_2_ ≤ 0.4. Attempts to withdraw NPPV are made if IPAP is decreased to 10–12 cmH_2_O, EPAP is 5 cmH_2_O, or daily use is less than 5 h. Weaning is considered successful if, for 72 h after withdrawal, patients are able to sustain spontaneous breathing without signs of respiratory distress, defined as the presence of at least two of the following: arterial pH < 7.35; RR > 30 breaths/min; PaO_2_ < 60 mmHg or arterial oxygen saturation measured by pulse oximetry (SpO_2_) < 90% at FiO_2_ ≥ 0.4; retraction of the intercostal spaces, use of accessory respiratory muscles, or thoracic–abdominal paradoxical movement; or decreased consciousness, agitation, or diaphoresis [30]. By contrast, when patients present with the aforementioned signs of respiratory distress after withdrawal, weaning is considered to have failed and NPPV is resumed.

Endotracheal intubation is considered if a patient has either arterial pH < 7.25 with PaCO_2_ > 20% greater than the baseline or PaO_2_ < 60 mmHg despite maximum tolerated supplemental oxygen, and if at least one of the following criteria is met: clinical signs suggestive of severely decreased consciousness (e.g., coma, delirium); excessive amount of respiratory secretions with weak cough; use of accessory respiratory muscles or thoracic–abdominal paradoxical movement; severe upper gastrointestinal bleeding with aspiration or vomiting; or severe hemodynamic instability, despite fluid repletion and use of vasoactive agents [29]. If a patient fulfills one of these criteria, the final decision for intubation is made by the attending physician, with the consent of the patient’s next of kin or other surrogate decision makers, as appropriate.

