### Data collection and definitions

At each study center, patient data will be collected using that center’s dedicated pseudonymous CRF, and the CRFs will be stored in locked file cabinets in areas with limited access. Data will be transmitted to the coordinating center whenever a patient dies or is discharged from the hospital, and follow-up data will be transmitted to the coordinating center when follow-up is complete. In addition, the coordinating center will have direct access to the cloud platform to extract the data related to the NPPV parameters. Before the data are exported into a computerized database at the coordinating center, two trained data collectors from the coordinating center will check the completeness and quality of information. Logical checks will be performed for missing data and to determine inconsistencies. If required, the data collector will contact the investigator by phone to validate or reformat the data for entry into the database. Then all data entry will be performed separately by two trained data collectors, and their work will be checked by another two collectors. Only the principal investigator and the data managers at the coordinating center will have access to the final database.

At enrollment, patients’ baseline characteristics will be recorded: demographics, medical history, history of NPPV use, history of steroids and/or inhalation therapy use, smoking status, spirometry (forced ventilatory capacity and forced expiratory volume in 1 s), Acute Physiology And Chronic Health Evaluation (APACHE) II score, vital signs (including heart rate, RR, arterial blood pressure, SpO_2_), dyspnea score, scale for the use of accessory muscles, Glasgow coma scale (GCS) score, arterial blood gases (including pH, PaO_2_, PaCO_2_, bicarbonates, and lactates), and routine laboratory tests (including hemoglobin, white blood cell count, platelet count, prothrombin time, partial thromboplastin time, creatinine, blood urea nitrogen, alanine aminotransferase, aspartate aminotransferase, and bilirubin).

At 2, 6, 24, and 48 h after randomization, vital signs, dyspnea score, scale for the use of accessory muscles, GCS score, supplemental oxygen flow, and arterial blood gases will be recorded.

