High-intensity NPPV is a novel therapeutic option which can be used to maximally decrease severely elevated PaCO_2_ to normal levels [25, 26]. In theory, high-intensity NPPV may be more efficient than low-intensity NPPV for augmenting alveolar ventilation and offsetting the extra dead space caused by the face mask, and reducing the inspiratory work of breathing and alleviating dyspnea in a way that provides more comfort during NPPV. Windisch et al. [27] reported that, in patients with stable hypercapnic COPD, improvements in PaCO_2_ levels, lung function, and breathing pattern were achieved using high-intensity NPPV. Dreher et al. [28] also directly compared high-intensity NPPV with the conventional approach of low-intensity NPPV in patients with stable hypercapnic COPD, and found that high-intensity NPPV was superior in terms of controlling nocturnal hypoventilation, thus improving dyspnea during physical activity, lung function, and health-related quality of life. However, whether high-intensity NPPV is superior to low-intensity NPPV in the treatment of AECOPD patients remains unclear. Hence, our aim is to verify whether high-intensity NPPV is more effective for correcting hypercapnia than low-intensity NPPV, thereby reducing the need for intubation and improving survival in AECOPD patients.

For low-intensity NPPV, we opted to adjust IPAP up to 20 cmH_2_O, according to patients’ tolerance, to obtain a possible target *V*_T_ of 10 mL/kg, regardless of whether normocapnia is achieved, a level confirmed by the literature and our routine clinical practice [13, 19, 29]. For high-intensity NPPV, we opted to adjust IPAP up to 30 cmH_2_O according to patients’ tolerance, to obtain a possible target *V*_T_ of 15 mL/kg [25, 26]. Importantly, the major target for the adjustment of IPAP is achieving normocapnia as far as possible [25]. The target *V*_T_ of 15 mL/kg is set to offset the extra dead space caused by the face mask over the *V*_T_ of 10 mL/kg in the low-intensity NPPV group, and precisely this level was chosen because the inner volume of the face mask is about 240–375 mL, which is approximately equal to 5 mL/kg [35]. To prevent ventilator-induced lung injury, we have set the upper limit for IPAP to 30 cmH_2_O, which is commonly considered safe [36].

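### In the high-intensity arm the only blood-gas trigger for lowering IPAP is PaCO2 below 35 mmHg, which in high-bicarbonate patients acts only after pH is well above normal

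*Protocol article*

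**What the plan says.** The section on high-intensity NPPV starts IPAP at 10 cmH2O and moves it in steps of 1–2 cmH2O up to 30 cmH2O, as tolerated, towards a tidal volume of 15 mL/kg of predicted body weight. It then sets the gas-exchange goal: "IPAP should be increased as much as possible to decrease PaCO_2_ to a normal level". The back-off is: "if PaCO_2_ decreases to less than 35 mmHg, IPAP should be decreased to achieve normocapnia". The Discussion gives the order of priority: "the major target for the adjustment of IPAP is achieving normocapnia as far as possible". The low-intensity arm has no such goal; its pressure is set "regardless of whether normocapnia is achieved".

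Under Study population, patients enter "with arterial pH < 7.35 and ≥ 7.25, and PaCO_2_ > 45 mmHg". Neither PaCO2 nor bicarbonate has an upper limit.

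Elsewhere the plan does use pH to judge the patient's state: at entry, and in the intubation criteria, one branch of which is "arterial pH < 7.25 with PaCO_2_ > 20% greater than the baseline". The blood gases recorded at baseline are "arterial blood gases (including pH, PaO_2_, PaCO_2_, bicarbonates, and lactates", and gases are repeated at 2, 6, 24 and 48 h.

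**The concern.** A back-off exists to catch over-ventilation. In a patient with normal bicarbonate, PaCO2 below 35 mmHg is a reasonable marker of it. In a patient with chronic hypercapnia and retained bicarbonate it is a late one, because pH is normal while PaCO2 is still well above 45 and becomes alkalaemic as PaCO2 approaches normal. The entry criteria admit such patients.

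For them, the rule asks for more pressure until PaCO2 is normal and asks for no reduction between 45 and 35 mmHg, whatever the pH. What is at stake is safety in the experimental arm only, since the control arm has no normocapnia target. The pH that would give the warning is on the same blood gas as the PaCO2.

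**Working it through.** The plan gives no figure on this point to reproduce. The check asks what pH an eligible patient has when the rule reaches its goal and when its back-off begins.

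**Inputs from the protocol.** Entry pH 7.25 to below 7.35 and entry PaCO2 above 45 mmHg (Study population); back-off below 35 mmHg (High-intensity NPPV).

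**Assumptions.** Normal PaCO2 is read as 35–45 mmHg, from the entry criterion and the back-off. The upper limit of normal pH is taken as 7.45. During titration bicarbonate falls by s = 0, 0.1 or 0.2 mmol/L per mmHg fall in PaCO2 (0, 1 or 2 per 10 mmHg). The protocol gives none of these slopes, so all three are shown.

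**Formulas.** [H+] = 10^(9 − pH) nmol/L and bicarbonate = 24 × PaCO2 / [H+]. At a later PaCO2 of P, with entry PaCO2 P0 and entry bicarbonate B:

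pH(P) = 9 − log10( 24 × P / (B − s × (P0 − P)) ).

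**Step 1: no slope needed.** The bicarbonate present at the time that puts pH at 7.45 is 24 × P / 10^1.55:

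- P = 45: 30.4 mmol/L
- P = 40: 27.1 mmol/L
- P = 35: 23.7 mmol/L

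Any higher bicarbonate means pH above 7.45 at that PaCO2. A slightly different solubility constant gives 30.2 in place of 30.4.

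**Step 2: worked patient.** Entry pH 7.30 and PaCO2 80: [H+] = 10^1.70 = 50.1, so B = 24 × 80 / 50.1 = 38.3 mmol/L.

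| Fall in bicarbonate per 10 mmHg | Bicarbonate at PaCO2 45 | pH at 45 | Bicarbonate at PaCO2 35 | pH at 35 |
|---|---|---|---|---|
| 0 | 38.3 | 7.55 | 38.3 | 7.66 |
| 1 | 34.8 | 7.51 | 33.8 | 7.60 |
| 2 | 31.3 | 7.46 | 29.3 | 7.54 |

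**Step 3: which entrants are affected.** Entry PaCO2 (mmHg) above which pH exceeds the stated value by the time PaCO2 is 45; the three figures are for falls of 0 / 1 / 2 mmol/L per 10 mmHg:

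| Entry pH | pH above 7.45 at PaCO2 45 | pH above 7.50 at PaCO2 45 |
|---|---|---|
| 7.25 | 71.3 / 79.4 / 94.5 | 80.0 / 90.7 / 110.9 |
| 7.30 | 63.6 / 68.5 / 76.9 | 71.3 / 78.3 / 90.2 |
| 7.35 (upper bound) | 56.7 / 59.3 / 63.6 | 63.6 / 67.8 / 74.6 |

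With s = 0 these are 45 × 10^(cut-off − entry pH); for example 45 × 10^0.15 = 63.6.

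**Step 4: who is not affected.** Entry pH 7.30 and PaCO2 50 (bicarbonate 23.9): pH reaches 7.45 only at PaCO2 35.4 / 32.9 / 29.3, at about the existing back-off or below it. Entry pH 7.30 and PaCO2 60 with fixed bicarbonate: pH is about 7.43 at PaCO2 45.

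**Step 5: what a pH limit of 7.50 would cost in separation.** Setting pH(P) = 7.50 gives P = (B − s × P0) / (24/10^1.50 − s), where 24/10^1.50 = 0.759. For the worked patient:

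- s = 0: 38.31 / 0.759 = 50.5, which is 5.5 mmHg short of 45
- s = 0.1: (38.31 − 8) / 0.659 = 46.0, which is 1.0 short
- s = 0.2: (38.31 − 16) / 0.559 = 39.9, already below 45, so nothing is lost

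**The case against.** The strongest reply is that normocapnia is the treatment under test. The Background defines high-intensity NPPV by it and argues that residual hypercapnia may itself do harm. A hard stop at pH 7.45 would replace that target in just the patients with the highest PaCO2: the worked patient would stop at 56.6, 52.6 or 46.8 mmHg. This objection stands, and it is why the fix leaves the target alone and changes only the back-off.

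Other limits exist. Tolerance, 30 cmH2O or the tidal-volume target may end titration before normocapnia. Operators are experienced, patients are watched at the bedside, and the DSMB reviews adverse events. The weaning section also lets pressure be lowered in any stable patient. As printed, its pH criterion is below 7.35, probably a slip, because the same section lists that value as a sign of distress. Even with the sign reversed, the clause permits a reduction and does not call for one when pH is high. These points reduce how often the problem arises, but none of these provisions makes pH a trigger.

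The article is condensed, and the trial organization section mentions an investigator manual, which could hold more bedside detail. But the article states the rule together with its own back-off, so the point concerns what is written.

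A reader might also infer that the 2-h PaCO2 endpoint is inflated by overshoot. That would need patients to fall from 80 to 45 mmHg within 2 h of starting at 10 cmH2O, and the document does not show that any do. Nor is it a fault that the article does not say whether easing pressure for pH is a per-protocol deviation; that detail is commonly left to the analysis plan.

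**Conclusion.** The point holds as a safety gap in the high-intensity titration rule. For patients whose bicarbonate is above about 30 mmol/L at PaCO2 45, the only written blood-gas back-off comes after pH has left the normal range: at PaCO2 35 the worked patient is at 7.54 to 7.66, depending on the bicarbonate slope. The direction is the same under all three slopes for that patient, but the size is not. At the steepest slope pH at PaCO2 45 is only 7.46, and a patient entering at pH 7.30 and PaCO2 70 would not yet have passed 7.45 there.

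The result rests on the assumed slopes, on reading normal PaCO2 as 35–45 mmHg, and on 7.45 as the upper limit of normal pH. The affected share cannot be estimated, because the document gives no baseline PaCO2 or bicarbonate distribution and no rate of reaching normocapnia.

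It would go too far to say that the rule drives every high-bicarbonate patient into alkalaemia, or that it undermines the trial's main result. The other limits may act first, and the intention-to-treat comparison of NPPV failure stays valid. The change is worth making, but the trial's conclusions do not hang on it.

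**What to change.** Keep normocapnia as the target and extend the existing back-off under High-intensity NPPV, for example:

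*IPAP is not increased further, and is decreased by 1–2 cmH2O, if PaCO2 is below 35 mmHg or arterial pH is above 7.50.*

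The 7.50 cut-off is a proposal for the sponsor to confirm; it has no source in the document. Date the change, record which rule each patient was treated under, and keep all randomized patients in the intention-to-treat analysis. If the rule is kept as it is, state this among the limitations in the Discussion.

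The change needs no extra blood gas, visit or patient. It does need an amendment to version 6 with approval at the participating centres. Recruitment began in December 2017, so two rules would exist within one arm. PaCO2 separation shrinks slightly in the affected patients, by the 5.5, 1.0 or 0 mmHg of Step 5 in the worked case. The effect on the intubation rate is unknown.

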### Low-intensity NPPV

In the low-intensity NPPV group, patients will undergo pressure-limited NPPV (e.g., NPPV in spontaneous/timed mode) with a conventional IPAP level. IPAP is initially set to 10 cmH_2_O and is continuously adjusted by increments and decrements of 1–2 cmH_2_O (up to 20 cmH_2_O), according to patients’ tolerance, to obtain a *V*_T_ of 10 mL/kg of PBW [13, 15, 19].

### NPPV implementation

NPPV will be performed by investigators with considerable experience. Both high-intensity and low-intensity NPPV will be provided using the same noninvasive ventilator with a cloud platform that can provide data transmission and exchange over a wireless network (Resmart GII Y-30 T, BMC Medical Co., Ltd., Beijing, China). An oro-nasal mask of the proper size (iVolve Full Face Mask BMC-FM, BMC Medical Co.; http://www.bmc-medical.com) will be the first choice, but a nasal mask (N4 Nasal Mask, BMC Medical Co.) may be used if a patient does not tolerate the oro-nasal mask. A disposable single-limb circuit will be used, and a leak port will be incorporated into the mask. Our standard procedures are described as follows.

In both groups, expiratory positive airway pressure (EPAP) is set at 5–8 cmH_2_O, the back-up respiratory rate (RR) is set to 10 breaths/min, rise time is set to 25–200 ms, and the inspiratory time is set at a minimum of 0.5 s and a maximum of 2.0 s. Supplemental oxygen is supplied through a port in the mask, with the flow rate adjusted to maintain an oxygen saturation between 90 and 95%.

All patients lie in a semi-recumbent position, with the head of the bed elevated to an angle of 30–45°. All patients included in the study will be encouraged to use NPPV as much as possible during the first 6 h after randomization and at least 10 h per day, and they will be rigorously monitored at bedside to ensure optimal NPPV use. Disconnection from the ventilator is allowed for short periods (to clear secretions, drink water, or eat food), but it is not scheduled.

A heated humidifier (H60 heated humidifier, BMC Medical Co.) is used to guarantee the delivered gas, with a 100% relative humidity at about 30–34 °C. Active drinking and expectoration of secretions should be encouraged. Possible complications related to NPPV (e.g., poor NPPV tolerance, asynchrony due to leaks, nasal/facial skin necrosis, conjunctivitis, sinus/ear pain, nasal/oral dryness, gastric distention, aspiration, hypotension, acute respiratory distress syndrome, pneumothorax, and claustrophobia) are systematically evaluated and alleviated as much as possible.

### NPPV weaning and failure

For all patients, the levels of IPAP and EPAP and the daily use of NPPV can be gradually decreased under conditions of clinical stability, defined as the presence of the following: the improvement or resolution of the underlying cause of AECOPD, RR < 25 breaths/min, heart rate < 110 beats/min, arterial pH < 7.35, and PaO_2_ > 60 mmHg at FiO_2_ ≤ 0.4. Attempts to withdraw NPPV are made if IPAP is decreased to 10–12 cmH_2_O, EPAP is 5 cmH_2_O, or daily use is less than 5 h. Weaning is considered successful if, for 72 h after withdrawal, patients are able to sustain spontaneous breathing without signs of respiratory distress, defined as the presence of at least two of the following: arterial pH < 7.35; RR > 30 breaths/min; PaO_2_ < 60 mmHg or arterial oxygen saturation measured by pulse oximetry (SpO_2_) < 90% at FiO_2_ ≥ 0.4; retraction of the intercostal spaces, use of accessory respiratory muscles, or thoracic–abdominal paradoxical movement; or decreased consciousness, agitation, or diaphoresis [30]. By contrast, when patients present with the aforementioned signs of respiratory distress after withdrawal, weaning is considered to have failed and NPPV is resumed.

Endotracheal intubation is considered if a patient has either arterial pH < 7.25 with PaCO_2_ > 20% greater than the baseline or PaO_2_ < 60 mmHg despite maximum tolerated supplemental oxygen, and if at least one of the following criteria is met: clinical signs suggestive of severely decreased consciousness (e.g., coma, delirium); excessive amount of respiratory secretions with weak cough; use of accessory respiratory muscles or thoracic–abdominal paradoxical movement; severe upper gastrointestinal bleeding with aspiration or vomiting; or severe hemodynamic instability, despite fluid repletion and use of vasoactive agents [29]. If a patient fulfills one of these criteria, the final decision for intubation is made by the attending physician, with the consent of the patient’s next of kin or other surrogate decision makers, as appropriate.

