**Fig. 2 Fig2:**
[figure not shown]
SPIRIT schedule of enrollment, intervention, and assessments. *APACHE* Acute Physiology And Chronic Health Evaluation, *NPPV* noninvasive positive pressure ventilation, *GCS* Glasgow coma scale *ICU* intensive care unit

The trial was designed in accordance with the fundamental principles set forth in the Declaration of Helsinki and the requirements established by Chinese legislation in the field of biomedical research for the protection of personal data and concerning bioethics. The protocol has reached version 6, in which there were no further changes. The approval of the final protocol by the ethics committee at each participating center was obtained before recruitment was initiated. For inclusion in the study, signed written informed consent will be obtained from the patients, patients’ next of kin, or other surrogate decision makers, if appropriate (see Additional file 2). The study was registered on December 7, 2016 at https://ClinicalTrials.gov with identification number NCT02985918.

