## Trial status

The HAPPEN study is currently recruiting patients. Recruitment began in December 2017. The expected duration of the study is 12 months. The final results will be published as soon as possible after the analysis is completed.

## Appendix 1

Investigators of the HAPPEN collaboration group (in alphabetical order by hospital):

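### The clinical-stability rule for reducing NPPV requires arterial pH below 7.35, the plan's own threshold for acidosis and distress; the inequality is almost certainly reversed

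*Protocol article*

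**What the plan says.** The section NPPV weaning and failure sets one step-down rule for both arms: "the levels of IPAP and EPAP and the daily use of NPPV can be gradually decreased under conditions of clinical stability". Stability is a list joined by 'and', with no 'at least' qualifier, so all five conditions must hold together: the cause of the exacerbation has improved or resolved, then "RR < 25 breaths/min, heart rate < 110 beats/min, arterial pH < 7.35", and finally PaO2 above 60 mmHg at FiO2 of 0.4 or less.

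The same paragraph then defines respiratory distress after withdrawal, which means weaning has failed and NPPV is resumed: "defined as the presence of at least two of the following: arterial pH < 7.35; RR > 30 breaths/min", followed by an oxygenation sign that begins "PaO_2_ < 60 mmHg or arterial oxygen saturation measured by pulse oximetry" and two groups of clinical signs.

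Study population makes the same pH range the acidosis needed for enrolment: "with arterial pH < 7.35 and ≥ 7.25".

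On status, Study design reports that "The protocol has reached version 6, in which there were no further changes", and Trial status says "The HAPPEN study is currently recruiting patients".

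**The concern.** A stability criterion should identify patients who have recovered enough to have support reduced. As printed, the pH item identifies patients who are still acidotic. It uses the value and direction that the article elsewhere uses to admit patients to the trial and to recognise failed weaning.

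What is at stake is a bedside threshold for lowering ventilatory support in a trial that is already recruiting at 27 wards. Taken literally, the rule could hold recovered patients on full support, or allow support to be reduced in patients who remain acidotic. Duration of NPPV is recorded and ventilator-free days within 28 days are a secondary endpoint, so the weaning rule has some bearing on what is measured. The rule does not define the primary endpoint and is identical in both arms, so no bias in the primary comparison is alleged.

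**Working it through.** The plan gives no figure to reproduce here. The check is a comparison of the article's own thresholds.

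**Step 1. Measurements that appear in both lists (NPPV weaning and failure).**

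| Measurement | Stability | Distress | Direction |
|---|---|---|---|
| Respiratory rate (breaths/min) | < 25 | > 30 | opposite |
| PaO2 (mmHg) | > 60 | < 60 | opposite |
| Arterial pH | < 7.35 | < 7.35 | same |

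Two of the three shared measurements reverse between the lists. pH is the exception.

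**Step 2. The pH item across its range, with the other four stability conditions taken as met.**

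| pH | Stable as printed (< 7.35) | Stable if corrected (≥ 7.35) | Distress signs contributed by pH |
|---|---|---|---|
| 7.25 | yes | no | 1 |
| 7.30 | yes | no | 1 |
| 7.34 | yes | no | 1 |
| 7.35 | no | yes | 0 |
| 7.40 | no | yes | 0 |
| 7.45 | no | yes | 0 |

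The two versions disagree everywhere. That follows from one being the negation of the other; what the table adds is which patients fall on which side.

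**Step 3. What the printed item implies.**

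- Entry requires 7.25 ≤ pH < 7.35, so every enrolled patient meets the pH item at enrolment. It cannot separate a stable patient from a newly enrolled one. It is one of five conditions and does not by itself permit step-down.
- A patient with pH of 7.35 or above fails the item and cannot be classed as stable, however well the other four conditions are met.
- The item has no lower bound. A pH below 7.25, the value used in the intubation rule of the same section, also satisfies it.
- A patient stepped down at pH below 7.35, with pH unchanged after withdrawal, already has one of the two signs that define distress.

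With pH ≥ 7.35 all four anomalies disappear, and stability becomes the complement of the entry and distress thresholds.

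**Step 4. Could this be a text-reading fault?** That is unlikely. The symbols ≤ and ≥ appear correctly elsewhere in the same section, and > is correct in the same sentence. Nothing else in the article states a different stability pH.

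**A smaller wording point in the same section.** The intubation rule reads naturally as a gas-exchange criterion (pH below 7.25 with PaCO2 more than 20% above baseline, or PaO2 below 60 mmHg despite maximum tolerated oxygen) together with at least one clinical criterion. The closing sentence, "If a patient fulfills one of these criteria, the final decision for intubation is made by the attending physician", is looser, because taken alone it lets a single criterion suffice. The pH finding does not depend on this.

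**The case against.** The printed inequality itself is hard to defend. The case on the other side is that it matters little.

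- **It is a one-symbol misprint that clinicians will read through.** Step-down is permissive and gradual, is carried out by experienced staff with close bedside monitoring, and NPPV is resumed if distress appears. In the high-intensity arm, IPAP is to be raised as far as possible to normalise PaCO2, which works against stepping down a hypercapnic, acidotic patient. These safeguards are real and limit the likely practical effect; they do not make the threshold right. The triggers for attempting withdrawal (IPAP 10–12 cmH2O, EPAP 5 cmH2O, or daily use under 5 h) contain no pH item, so the stability rule is the only stated pH check before withdrawal.
- **The sites work from protocol version 6, which is not shown.** This stands. The error is established for the article only, and the check of version 6 must come first. The article nevertheless states the rule, and states it wrongly, so this is not a detail left to the full protocol.
- **The intubation sentence is editorial.** Largely so. Its reference to one criterion can be read as pointing back to the clinical list just before it. It is kept only as a minor clarification.

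**Conclusion.** The stability condition is wrong as written and should be corrected. The direction of the error follows from the article's own definitions and needs no outside source. The exact intended value (≥ 7.35 rather than > 7.35) is inferred and is for the investigators to confirm.

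Among patients who meet the other four conditions, the printed item classifies every pH value the wrong way round. How many patients that touches cannot be computed from the article, and it depends on whether version 6 carries the same slip and on whether clinicians follow the rule literally. Sample size and planned analysis are unaffected.

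**What to change.** 1. Change the stability condition to arterial pH ≥ 7.35, with the investigators confirming the value.
2. Check whether protocol version 6, as held at the sites, has the same inequality.
3. Notify all 27 centres. If version 6 is wrong, the notice corrects it and the correction also goes to the ethics committees that approved it. If version 6 is right, the notice need only say that the published article has a misprint and that the site protocol governs.
4. As a minor clarification, align the closing intubation sentence with the rule before it: a gas-exchange criterion and at least one clinical criterion, after which the attending physician decides.

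The cost is one symbol, one clarified sentence, a document check and a notice. Endpoints, analysis and data collection do not change.

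### As printed, EPAP 5 cmH2O alone triggers an NPPV withdrawal attempt in a stable patient, although EPAP 5 is an allowed setting from the start and IPAP may not have been tapered

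*Protocol article*

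**What the plan says.** All places are in the protocol article.

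- **NPPV weaning and failure, reduction.** IPAP, EPAP and daily use "can be gradually decreased under conditions of clinical stability". Stability is defined by improvement of the underlying cause, respiratory rate, heart rate, arterial pH and oxygenation. The list contains no IPAP or PaCO2 condition.
- **NPPV weaning and failure, withdrawal.** The next sentence says that attempts to "withdraw NPPV are made if IPAP is decreased to 10–12 cmH_2_O, EPAP is 5 cmH_2_O, or daily use is less than 5 h".
- **NPPV implementation.** In both groups "expiratory positive airway pressure (EPAP) is set at 5–8 cmH_2_O". Patients are encouraged to use NPPV "at least 10 h per day".
- **High-intensity NPPV.** IPAP starts at 10 cmH2O and is "continuously adjusted by increments and decrements of 1–2 cmH_2_O (up to 30 cmH_2_O").
- **Low-intensity NPPV.** IPAP starts at 10 cmH2O and is "continuously adjusted by increments and decrements of 1–2 cmH_2_O (up to 20 cmH_2_O").

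**The concern.** The withdrawal rule treats its two pressure items differently. IPAP has to have been *decreased to* its end-point, so the starting value of 10 cmH2O does not count by accident. EPAP only has to *be* 5, and 5 is the bottom of the range allowed from the first hour. A patient set at EPAP 5 throughout satisfies that item without any weaning step.

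Inspiratory pressure is what the trial randomizes. Read literally, the rule lets a stable patient go from the full randomized IPAP to a withdrawal attempt, although the sentence before it describes a gradual reduction. Sites at 27 wards could also apply it differently: some literally, some by reading the two pressures jointly. What is at stake is the duration of exposure to the assigned pressure and uniform conduct across sites.

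**Working it through.** The plan gives no figure to reproduce. The check is a logical one: which allowed settings meet the rule under each reading?

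**Inputs**

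- IPAP, whole cmH2O: 10–30 (21 values) in the high-intensity arm and 10–20 (11 values) in the low-intensity arm, from the two arm sections.
- EPAP, whole cmH2O: 5–8 (4 values) in both arms, from NPPV implementation.
- Daily use: two states, below 5 h, or meeting the target of 10 h or more.
- The patient is taken to be clinically stable. The withdrawal sentence does not repeat that condition, so carrying it over from the preceding sentence favours the protocol.

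**Conditions.** A: IPAP is 10–12. B: EPAP is 5. C: daily use is below 5 h.

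**Number of settings.** High: 21 × 4 × 2 = 168. Low: 11 × 4 × 2 = 88.

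| Reading | High (of 168) | Low (of 88) |
|---|---|---|
| A or B or C (as printed) | 114 | 64 |
| (A and B) or C | 87 | 47 |
| A and B and C | 3 | 3 |
| B the only item met, as printed | 18 | 8 |

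Derivation for the high arm:

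- C holds in 21 × 4 = 84 settings. Where C fails, A or B holds in 3 × 4 + 21 − 3 = 30. As printed: 84 + 30 = 114.
- With A and B required jointly, only 3 settings are added to C: 84 + 3 = 87.
- B alone: 21 − 3 = 18, which are IPAP 13 to 30 at EPAP 5.

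For the low arm the same steps give 44 + (12 + 11 − 3) = 64, then 44 + 3 = 47, and 11 − 3 = 8, which are IPAP 13 to 20 at EPAP 5.

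**Distance from the upper end of the IPAP end-point (12 cmH2O) when EPAP 5 alone triggers**

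- High-intensity maximum: 30 − 12 = 18 cmH2O.
- Low-intensity maximum: 20 − 12 = 8 cmH2O.
- A patient at IPAP 16 in either arm: 16 − 12 = 4 cmH2O.
- If A and B are required together: 0 by this route.

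**What the joint reading changes.** High: 114 − 87 = 27 settings no longer trigger. These are the 18 EPAP-only settings plus 3 × 3 = 9 with IPAP 10–12 and EPAP 6–8. Low: 64 − 47 = 17 = 8 + 9.

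**What it leaves.** The daily-use route still triggers at IPAP above 12 in 18 × 4 = 72 settings (high) and 8 × 4 = 32 (low).

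These counts describe what the wording permits. They are not frequencies of patients.

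**The case against.** The strongest reply is that the context settles the meaning. The preceding sentence names IPAP, EPAP and daily use as the things to be lowered, and the withdrawal sentence gives an end-point for each in the same order, so EPAP 5 reads naturally as the end of a taper. The staff are experienced, the article is a condensed text, and an investigator manual that is not shown may state the rule properly. Withdrawal is only an attempt: patients are judged over 72 h and NPPV resumes if distress appears. This stands as a reason to think that *or* is a slip and that the consequence is small. It does not change what is printed, and nothing in the article says that the pressures apply jointly.

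A reader might infer more than the documents support:

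- **A conflict with the normocapnia target.** The high-intensity section says "IPAP should be increased as much as possible to decrease PaCO_2_ to a normal level", and the Discussion says "the major target for the adjustment of IPAP is achieving normocapnia as far as possible". Those statements govern titration. Weaning lowers IPAP in all stable patients with no PaCO2 condition, whichever operator is used, so any tension does not come from the *or*.
- **Bias by arm.** The maxima differ (18 against 8 cmH2O), but the rule and the EPAP range are the same in both arms, and the maxima apply only at the IPAP ceilings.
- **An effect on the primary endpoint.** A failed withdrawal leads back to NPPV, and intubation has its own criteria.
- **An effect on ventilator-free days.** The article does not define that endpoint as counting days on NPPV.
- **A number of weaning steps skipped.** The 1–2 cmH2O step is given for titration. No weaning step is stated.
- **A lasting difference between starting EPAP settings.** A stable patient at EPAP 6 may be lowered to 5 and then meets the same trigger.

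**Conclusion.** The point holds as a minor defect in a stated operating rule. EPAP 5 alone is enough for a withdrawal attempt in a stable patient, at any IPAP from 13 to 30 cmH2O (high-intensity) or 13 to 20 cmH2O (low-intensity), and no other condition in the article closes that route. The conclusion rests on reading *or* as written and on EPAP 5 being usable from the start. That the investigators meant a joint condition is an inference.

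The consequence that can be stated is possible early loss of exposure to the randomized pressure. It cannot be sized further, because the share of patients set at EPAP 5 and their IPAP at the time of stability are not given.

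**What to change.** Replace the withdrawal sentence with one to this effect: *in a clinically stable patient, withdrawal of NPPV is attempted once IPAP has been brought down to 10–12 cmH2O and EPAP is 5 cmH2O, or once daily use has been deliberately reduced below 5 h as part of weaning.* Apply it identically in both arms, and have the investigators confirm that this is the operator they intended.

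The word *deliberately* prevents poor use against the 10 h target from counting as readiness to withdraw. The rewording removes the EPAP-only route. The hours route remains as a separate form of taper and does not itself guarantee a lowered IPAP.

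The cost is one protocol sentence and a letter to sites. Some patients may stay on NPPV slightly longer, including those at IPAP 10–12 whose EPAP is still 6–8. No new data are needed, since pressures and daily use already reach the cloud platform (Data collection and definitions).
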